## Abstract

**Background:**

Large skull defects present a reconstructive challenge. Conventional cranioplasty options include autologous bone grafts, vascularized bone, metals, synthetic ceramics, and polymers. Autologous options are affected by resorption and residual contour deformities. Synthetic materials may be customized via digital planning and 3D printing, but they all carry a risk of implant exposure, failure, and infection, which increases when the defect is large. These complications can be a threat to life. Without reconstruction, patients with cranial defects may experience headaches and stigmatization. The protection of the brain necessitates lifelong helmet use, which is also stigmatizing.

**Objective:**

Our clinical trial will formally study a hybridized technique's capacity to reconstruct large calvarial defects.

**Methods:**

A hybridized technique that draws on the benefits of autologous and synthetic materials has been developed by the research team. This involves wrapping a biodegradable, ultrastructured, 3D-printed scaffold made of medical-grade polycaprolactone and tricalcium phosphate in a vascularized, autotransplanted periosteum to exploit the capacity of vascularized periostea to regenerate bone. In vitro, the scaffold system supports cell attachment, migration, and proliferation with slow but sustained degradation to permit host tissue regeneration and the replacement of the scaffold. The in vivo compatibility of this scaffold system is robust—the base material has been used clinically as a resorbable suture material for decades. The importance of scaffold vascularization, which is inextricably linked to bone regeneration, is underappreciated. A variety of methods have been described to address this, including scaffold prelamination and axial vascularization via arteriovenous loops and autotransplanted flaps. However, none of these directly promote bone regeneration.

**Results:**

We expect to have results before the end of 2023. As of December 2020, we have enrolled 3 participants for the study.

**Conclusions:**

The regenerative matching axial vascularization technique may be an alternative method of reconstruction for large calvarial defects. It involves performing a vascularized free tissue transfer and using a bioresorbable, 3D-printed scaffold to promote and support bone regeneration (termed the *regenerative matching axial vascularization* technique). This technique may be used to reconstruct skull bone defects that were previously thought to be unreconstructable, reduce the risk of implant-related complications, and achieve consistent outcomes in cranioplasty. This must now be tested in prospective clinical trials.

**Trial Registration:**

Australian New Zealand Clinical Trials Registry ACTRN12620001171909; https://tinyurl.com/4rakccb3

**International Registered Report Identifier (IRRID):**

DERR1-10.2196/36111

## Introduction

### Background

Cranioplasty, as a procedure for reconstructing cranial defects, has been around for thousands of years. Despite significant advances in technology and extensive research into bone biology, the reconstruction of the calvarium still poses a significant challenge for surgeons [1,2]. Since the early 1900s, autologous bone grafts have been considered the gold standard, acting as readily available donor materials with marked strength, elasticity, assured biocompatibility, and the ability to provide adequate cosmesis [3]. Despite this, autologous bone grafts are not without complications, including bone flap resorption, and graft failure rates of up to 35% have been reported [4-7]. Other autologous bone grafts (eg, those in the form of banked allografts or those made of bone harvested from other anatomical locations) have also been shown to result in increased donor site morbidity and higher rates of graft failure.

These issues with autologous bone grafts have prompted research into suitable synthetic alternatives; metals, synthetic ceramics, and polymers are all advantageous in different ways but have significant fallbacks that relate to infection, malleability, and in situ inflammatory or exothermic reactions [8,9]. A bioresorbable composite scaffold comprised of polycaprolactone and tricalcium phosphate (PCL-TCP) has already been shown to be effective in various bone engineering platforms [7,10-13]. Further, 3D computed tomography (CT) modeling has revolutionized the customization of these osteoconductive scaffolds, enabling their seamless integration into skull defects, with aesthetic cranial contouring. Osteoinduction is a process whereby osteoprogenitor cells differentiate into osteoblasts and therefore is crucial in osteogenesis. Within PCL-TCP scaffolds, osteoinduction can be enhanced through the addition of biological additives (eg, bone morphogenetic protein-7) or cellular approaches (eg, the use of mesenchymal osteoprogenitor stem cells) that have been shown to augment bone growth [14-18].

The success of these cellular impregnation techniques for promoting acceptable osteogenesis has been shown to be directly linked with the vascularity of the constructs used [13,18]. The utilization of flap-based tissue with dependable axial vascularization (eg, based on a known arteriovenous system) not only enhances angiogenesis but also provides a specific tissue type that matches the intended regeneration along with corresponding progenitor cells [19]. Axial vascularization via a corticoperiosteal flap to stimulate bone regeneration is an example of regenerative matching axial vascularization (RMAV) [20]. The experimental application of this theory with corticoperiosteal flaps has been implemented in cases of critical long bone defects, with the results indicating enhanced bone regeneration and scaffold integration [21-23].

Throughout the literature, there is a clear consensus that an ideal cranioplasty graft should have the following: (1) long-term mechanical protection for the brain and meninges until the host bone regenerates, (2) acceptable cosmetic contouring, and (3) graft materials that promote bone growth through osteoconductive and osteoinductive mechanisms that are governed by degradation kinetics and biological interactions. Moreover, if the prosthesis remains, it should not cause undue complications or patient inconveniences.

The composite PCL-TCP scaffold acts as a synthetic analogue of two major bone constituents—hydroxyapatite and collagen. As cranioplasty materials, PCL-TCP fulfill the above criteria by retaining strength and promoting osteoconduction over extended remodeling periods via consistent degradation mechanics and with minimal adverse effects. As a consequence of advancements in tissue engineering, the demand for customizable implants is understandably intensifying. This case highlights the potential of harnessing emerging biomedical technologies and 3D tailoring to meet individual and specific clinical needs.

In a case report published by Yogishwarappa et al [24] in 2016, the authors utilized a 3D-printed PCL-TCP scaffold with iliac crest stem cells to reconstruct a craniotomy defect. The authors described good bone growth at 18 months but did not quantify this result via CT imaging, which has traditionally been the case in preceding animal studies. This case went further by incorporating axial vascularization techniques with strategies for the targeted regenerative matching of tissue types and progenitor cells.

Osteoinduction and, as a consequence, osteogenesis are intricately linked to angiogenesis in normal fracture healing [25]. Corticoperiosteal tissue from the medial femoral condyle can provide a vascularized source of tissue rich in osteogenic progenitor cells. Studies have shown that specific osteoprogenitor cells, such as those in periosteal tissue, are stimulated by growth factors to differentiate and form bone [26]. As a result, scaffolds are subject to the uniform delivery of host-derived growth factors, mesenchymal stem cells, and an optimal extra-cellular environment, of which all are essential for bone regeneration.

Investigations into periosteal flaps as sources of axial vascularization are well documented in animal models. Nau et al [22] compared periosteal flaps with a tricalcium phosphate scaffold that did or did not have bone marrow–derived mononuclear cells to a periosteal flap alone. These were used in rat femurs with critical size defects. The periosteal flap with tricalcium phosphate and marrow cells had a significant increase in new bone formation, vascularization and strength radiographic, histological, and biomechanical outcomes at 4 weeks. More recently, Sparks et al [20] combined a pedicled corticoperiosteal flap, which was based on the anterior tibial vessels, with a PCL-TCP scaffold to bridge 3- and 6-cm tibial segmentectomies. The radiological and histological outcomes demonstrated new bone regeneration and excellent scaffold integration, with the complete bridging of both defects at 12 months.

The research by our group at the Centre for Regenerative Medicine (Queensland University of Technology, Brisbane, Australia) has focused on the reconstruction of critical-sized bone defects for more than 1 decade [13,17,27]. In particular, our work has focused on the bench-to-bedside translation of tissue-engineered bone replacements that are biodegradable, ultrastructured composite scaffolds made of medical-grade PCL-TCP (mPCL-TCP) [28]. In vitro, this scaffold system supports cell attachment, migration, and proliferation with slow but sustained degradation to permit host tissue regeneration and the replacement of the scaffold [29]. The in vivo compatibility of this scaffold system is robust [30,31], and this system may be used alongside the use of growth factors, such as recombinant human bone morphogenic protein-7 (rhBMP-7), that are known to promote the regeneration of bone. Importantly, the mPCL-TCP scaffold has been extensively evaluated in preclinical studies with a validated model of a large animal with a critical-sized bone defect that was developed by our group [13]. Our research using this model has shown that this scaffold system, when used alongside rhBMP-7 for a 3-cm, critical-sized long bone defect, is highly regenerative with respect to bones [13].

Although osteoinductive scaffolds have been trialed clinically by a number of authors [32-35], limitations in preclinical work that prevent the mainstream application of this approach remain. Scaffold vascularization, which is inextricably linked to bone regeneration, remains key, and its importance is generally underappreciated [18]. A variety of methods have been investigated to address this issue, including the prevascularization of scaffold prior to transplantation, vessel-based approaches for axial vascularization (arteriovenous loops and associated variations), and flap-based approaches for axial vascularization (muscle flaps, periosteal flaps, etc). Clearly, the ideal method for vascularizing a scaffold would also promote bone regeneration.

The regenerative capacity of vascularized corticoperiosteal tissue is well recognized [36,37]. It has a robust blood supply, and potential donor sites for distant transfer are plentiful [19]. For uniform scaffold vascularization, an intrinsic approach is considered key [38]. However, to date, a combined intrinsic and flap-based approach to scaffold vascularization that also exploits the innate autologous regenerative capacity of corticoperiosteal tissue for bone regeneration has not been explored. We define the coalescence of these concepts as RMAV, whereby a corticoperiosteal flap is used to vascularize scaffold intrinsically and also produce bone.

Between 2016 and 2018, we undertook a preclinical study that evaluated the concept of RMAV by using a corticoperiosteal flap from a sheep’s hind limb and a 3D-printed mPCL-TCP scaffold to reconstruct 6- and 3-cm intercalary defects of the tibia [20]. This technique was compared against existing control data sets for this animal model. Control groups were reconstructed with autologous bone grafts alone, were reconstructed with mPCL-TCP scaffolds alone, or were left unreconstructed [20]. The regenerative matching approach resulted in the enhanced volume of regenerate bone, as shown on plain x-ray and micro-CT images [20], and equivalent biomechanical torsional stiffness when compared to the approach using bone grafts alone. In December 2019, we performed a first-in-human case study of applied RMAV, wherein a 3D-printed mPCL-TCP scaffold with rhBMP-7 and vascularized corticoperiosteal flaps was used to successfully perform a reconstruction of a large calvarial defect that had failed to heal after conventional cranioplasty [39]. This work builds on our experiences with bone defect reconstructive research, and it will involve the regenerative matching technique.

Given these successes in preclinical research and our first-in-human case, we feel that the logical next step for the emerging RMAV technique should be a robust feasibility clinical trial examining the behavior of the mPCL-TCP implant and postimplantation bone healing. Once appropriate outcome measures are clearly defined, it may then be appropriate to proceed to a randomized clinical trial in which RMAV is compared to other clinical techniques for a given bone defect.

### Objectives

#### Hypothesis

The use of an mPCL-TCP scaffold, in conjunction with a corticoperiosteal tissue transfer, is a safe and effective approach to reconstructing critical-sized bone defects in the calvarium.

#### Primary and Secondary Objectives

The primary objectives of our trial are to (1) determine the feasibility and efficacy of using an mPCL-TCP scaffold, in conjunction with a vascularized corticoperiosteal tissue transfer, for the reconstruction of calvarial bone and (2) determine the clinically relevant functional outcomes that follow the reconstruction of an acquired calvarial defect by using an mPCL-TCP scaffold in conjunction with a vascularized corticoperiosteal tissue transfer.

The secondary objective is to collect data to allow for the later evaluation of the cost-effectiveness of this approach and a view of its applications across a broader range of clinical situations.

## Methods

### Study Design

Our study will be a single-arm feasibility trial that evaluates the outcomes of using an mPCL-TCP scaffold, in conjunction with a vascularized corticoperiosteal tissue, in participants with acquired defects of the calvarial bones of the skull resulting from trauma, malignancy, or infection. The study will capture data that will be used to inform the design of future clinical trials in this area.

The mPCL-TCP scaffold that will be used in the study will be manufactured by the trial sponsor—Osteopore International Pte Ltd (Singapore). Osteopore products are made of a US Food and Drug Administration–approved polymer (K051093) called *polycaprolactone*, which is bioabsorbable, is malleable, is slow to degrade, and possesses mechanical strength that is similar to that of trabecular bone. The product will be manufactured by using 3D printing technology that is precise and allows for the customization of shape and geometry. The unique, 3D-printed, biomimetic microarchitecture of the 3D scaffolding, which is contained within Osteopore products, allows for the infiltration of cells and blood vessels, of which both play a key role in wound healing and tissue repair.

### Study Setting

The study will be an open-label, single-arm feasibility trial that will be jointly coordinated by the investigators at the Princess Alexandra Hospital (PAH) in Woolloongabba (Queensland, Australia), the Herston Biofabrication Institute, the Australian Centre for Complex Integrated Surgical Solutions at the Translational Research Institute (Queensland, Australia), and the Centre for Regenerative Medicine at the Institute of Health and Biomedical Innovation in Kelvin Grove (Queensland, Australia). With the aim of calvarial reconstruction, the study population will include any patient with a calvarial defect that is amenable to reconstructive approaches that involve using the Osteopore implant, following discussions by the multidisciplinary team (MDT) of investigators.

### Eligibility Criteria

#### Inclusion Criteria

Our inclusion criteria are as follows:

Acquired defect of the calvarium that is suitable for reconstruction by using a PCL-TCP scaffold system and performing a corticoperiosteal tissue transferPatients aged >18 years and <55 yearsPatients aged >55 years may still be eligible for the trial after an assessment by and at the discretion of the investigators, and documentation to this effect will be provided by the clinic for the trial documents pertaining to such patientsPatients who are willing and able to comply with the study requirementsPatients who are eligible for undergoing magnetic resonance imaging (MRI; ie, no implanted metal or metal devices and no history of severe claustrophobia)Patients or their guardians are capable of providing valid informed consent

#### Exclusion Criteria

Our exclusion criteria are as follows:

Active infection at the time of study inclusion (in chronic infection cases, active infections may manifest as the result of a failed trial of being taken off antibiotics)Patients or their guardians are unwilling or unable to provide fully informed consentPatients with a known history of immunodeficiency, including a history of HIV, concomitant systemic corticosteroid therapy, chemotherapy, synchronous hematological malignancy, or other causes of a secondary or primary immunodeficiencyPatients with a known severe concurrent or intercurrent illness (eg, a cardiovascular, respiratory, or immunological illness; psychiatric disorders; alcohol or chemical dependence; or possible allergies [including allergy to polycaprolactone]) that would, in the opinion of the primary investigator, compromise their safety or compliance or interfere with the interpretation of study resultsWomen who are currently pregnant, are breastfeeding, or are planning to become pregnant within 2 years after the reconstruction surgeryWomen of childbearing potential who are not using an appropriate contraceptive methodPatients who are ineligible for undergoing MRIPatients with a life expectancy of <36 months.Patients who are unable or unwilling to comply with the study requirements

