### Recruitment

As a part of their clinical management, patients with acquired calvarial defects from the neurosurgery clinic or the skull base/head and neck clinic at the PAH will be reviewed as candidates for cranial reconstruction via the Osteopore implant by the MDT. Referrals to this process will be accepted from throughout Queensland via standard pathways, and national out-of-catchment referrals will be considered for special circumstances in which the PAH has unique expertise. The specific conditions assessed may include acute and subacute pathologies (major acute fractures with bone loss, bone malignancy, etc) or chronic pathologies (osteomyelitis, osteoradionecrosis, etc).

The relevant specialties that will be involved in the MDT review and decision-making process include infectious diseases, plastic and reconstructive surgery, neurosurgery, infectious diseases, and engineering. The MDT will determine the best treatment option for each patient. Should cranial reconstruction by using an Osteopore implant be recommended by the MDT, the patient’s treating specialist will discuss the case with the coordinating principal investigator, and the extent to which the potential participant satisfies the trial’s inclusion and exclusion criteria will be determined collaboratively. Written informed consent will be obtained following the MDT’s decision and prior to the conduct of the cranioplasty. Informed consent must be completed prior to any study-related activities.

Patients will be followed up for at least 24 months from the time of initial reconstruction. Given that the PAH collectively sees around 5 patients per year with significant bone defects, the recruitment phase will take place over 2 to 3 years to recruit a total of 10 patients for the feasibility analysis.

In addition to the prospective recruitment pathway detailed above, patients who have undergone cranioplasty via the Osteopore implant may also be recruited into the study at the discretion of the sponsor and coordinating principal investigator.

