### Analysis

All patients who are registered for the trial will be accounted for in the (intention-to-treat) analysis. For retrospectively recruited patients, all data points may not be available for all assessments, or data collection may have occurred outside of the trial-specific window (eg, CT data are available for the 9-month follow-up but are not available for the 12-month follow-up). In such cases, these subjects will not be evaluated for a particular analysis unless the number of data points required for the analysis is enough, or a trend can be extrapolated from the data that were collected outside of the trial-specified window.

A quantitative analysis that relates to the evaluation of the cost-effectiveness of this approach will not be undertaken as a part of this study, as the data set will most likely be too small to achieve statistical significance. Instead, the outcome measures that have an impact on the financial burden for treating patients will be combined with data from other similar trials that are conducted in the future, and the analysis of health economics data will be undertaken at that point.

Statistical analyses of descriptive statistics for the demographic, primary, and secondary outcomes at each time point will be conducted. A comparison analysis of the questionnaire results at each time point and a univariate Cox regression analysis of the time to weight-bearing for the affected limbs will be performed due to the small sample size. Statistical significance will be defined as *P*<.05. Data will be analyzed by using SPSS for Windows version 22 (IBM Corporation).

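### For patients recruited after cranioplasty, the active-infection exclusion is timed after the implant, so read literally it can remove a treatment outcome from the cohort

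*Protocol article*

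**What the plan says.** The Exclusion Criteria rule out "Active infection at the time of study inclusion". The Inclusion Criteria require that the patient can have MRI, explained as "no implanted metal or metal devices and no history of severe claustrophobia", and MRI ineligibility appears again as an exclusion.

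Recruitment describes two routes.

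- On the main route, the multidisciplinary team recommends the implant, and then "the extent to which the potential participant satisfies the trial’s inclusion and exclusion criteria will be determined collaboratively". Consent and this check come before surgery.
- On the second route, "patients who have undergone cranioplasty via the Osteopore implant may also be recruited into the study", at the discretion of the sponsor and the coordinating principal investigator. No number or cap is given, and no date is named at which the criteria are judged for these patients.

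Follow-up is counted from surgery on either route: "Patients will be followed up for at least 24 months from the time of initial reconstruction".

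The Analysis section states: "All patients who are registered for the trial will be accounted for in the (intention-to-treat) analysis". What it adds about retrospectively recruited patients concerns missing or off-window data. The section on avoiding and limiting bias says that the eligibility criteria keep selection bias to a minimum.

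**The concern.** A baseline criterion should describe the patient before treatment. On the main route the infection rule does so. On the second route enrolment comes after time 0, so the same words can describe what happened to the implant. A patient with an active implant infection on the enrolment date would then be refused because the treatment had gone badly.

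The intention-to-treat statement cannot repair this, since it covers only those registered. An analysis plan cannot repair it either, because the patient is not in the data.

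This matters here because the Abstract says of synthetic cranioplasty materials that "they all carry a risk of implant exposure, failure, and infection", the hypothesis is that the approach is safe and effective, and the Discussion offers the results as baseline data for comparison with other implants. With 10 patients and no control arm, one or two missing failures would change the impression given.

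The problem is separate from the discretion over who is invited. Inviting every already-operated patient consecutively would still leave the infection rule to turn some away.

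**Working it through.** **The plan's own figure.** The only numerical basis for the sample size is accrual: about 5 patients a year over 2 to 3 years. 5 × 2 = 10 reproduces the stated total, and 5 × 3 = 15 is the upper end of the pool. There is no power calculation to check, and the point does not depend on one.

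**Where the timing bites.**

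| Step | Recruited before surgery | Recruited after surgery |
|---|---|---|
| Time 0 for follow-up | reconstruction | reconstruction |
| Study inclusion | before time 0 | after time 0 |
| Active infection at inclusion | baseline feature | may be an implant outcome |
| Implanted metal | baseline feature | outcome only if a failed implant was replaced with metal |

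**How large could it be?** This is an illustration. Three inputs are assumptions, because the article does not give them:

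- p, the true rate of infection or failure: 10%, 20% and 35%. The top value is the figure the Introduction reports for autologous graft failure. It is not a rate for this implant.
- k, the number of the 10 patients who were already operated: 0, 3 or 5.
- s, the share of failures among already-operated patients that leads to exclusion at enrolment: 0.5 or 1.

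Formulas:

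- Failure rate among the already-operated patients who are enrolled: r = p(1 − s)/(1 − ps)
- Expected observed rate: [(10 − k)p + k·r]/10
- Chance of seeing no failure: (1 − p)^(10−k) × (1 − r)^k

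Worked case, p = 20%, k = 3:

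- s = 1: r = 0, and the observed rate is (7 × 0.20)/10 = 14%.
- s = 0.5: r = 0.10/0.90 = 0.111, and the observed rate is (1.40 + 0.333)/10 = 17.3%.

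Expected observed rate with k = 3:

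| True rate p | s = 0.5 | s = 1 |
|---|---|---|
| 10% | 8.6% | 7.0% |
| 20% | 17.3% | 14.0% |
| 35% | 30.9% | 24.5% |

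With k = 5 and s = 1, a true 20% would be observed as 10%.

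Chance of reporting no failure in 10 patients at p = 20%:

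- No selection: 0.8^10 = 10.7%
- k = 3, s = 0.5: 0.8^7 × 0.889^3 = 14.7%
- k = 3, s = 1: 0.8^7 = 21.0%
- k = 5, s = 1: 0.8^5 = 32.8%

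With k = 0 the observed rate equals p.

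**The case against.** A reader might infer that all the exclusion criteria are judged at study inclusion, and that any infected or exchanged implant makes the patient ineligible. The document does not support that. The timing phrase belongs to the infection criterion alone, and the pregnancy criterion, for example, is tied to the reconstruction surgery. No criterion mentions a removed, exchanged or failed implant. An exchange matters only indirectly, if the replacement contains metal. An infection that has resolved, a removal without replacement and a non-metal exchange are not excluded by the text. The s = 1 figures are therefore a worst case.

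It can also be argued that pre-operative status was meant throughout. The first inclusion criterion speaks of a defect suitable for reconstruction, which hardly fits a skull already reconstructed. The infection criterion goes on to discuss chronic infection and stopping antibiotics, and Table 1 puts infection management at enrolment, before reconstruction. This reading is possible, and the full protocol may state it. Nothing in the article does, however, and the one phrase that fixes a date points to inclusion.

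Two further points stand in part. Infection and failure rates are not named primary end points, although imaging is planned to identify complications and the hypothesis concerns safety. The discretion over who enters is also a selection problem of its own and may be the larger one, but removing it would leave this one in place.

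**Conclusion.** The point holds in a limited form. As worded, the infection exclusion lets an outcome decide eligibility for patients recruited after cranioplasty, and on that route it works against the article's claim that the criteria minimise selection bias. The metal rule could add to this only through replacement of a failed implant with metal. Patients recruited before surgery are unaffected.

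The direction is known: on this route the bias favours the technique. The size is not known. At an assumed true rate of 20% with 3 already-operated patients, the expected observed rate lies between 14% (all earlier failures screened out) and 20% (none), with 17.3% if half are. These figures show what could happen and are not estimates for this trial.

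**What to change.** Add a statement to the eligibility section that, for already-operated patients:

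- the baseline clinical criteria (infection, suitability of the defect, comorbidity, metal implants) are judged from records as at the date of reconstruction, time 0;
- infection, exposure, removal or exchange after time 0 is an outcome and not a reason for exclusion;
- consent and willingness to comply are still judged at enrolment, since they cannot be back-dated;
- a patient who can no longer safely have MRI stays in the cohort, with that scan recorded as not done.

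Report how many earlier scaffold-plus-flap patients were not entered, with reasons, and show results separately for patients recruited before and after surgery.

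The cost is a short addition to the text and a short chart review. The sample size stays at 10. The reported rates may become less favourable. If every already-operated patient were also entered consecutively, the expected observed rate would equal p and this distortion would be gone.
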